# The use and protective effects of transcutaneous electrical acupoint stimulation during abdominal surgery: study protocol for a multicenter randomized parallel controlled trial

**DOI:** 10.1186/s13063-019-3558-2

**Published:** 2019-07-29

**Keywords:** Transcutaneous electrical acupoint stimulation, Anesthesia management, Gastrointestinal surgery, Organ protection

## Abstract

**Background:**

Acupuncture-balanced anesthesia has been found to offer protective benefits. Electrical stimulation at certain acupoints can potentially promote perioperative gastrointestinal function recovery. The purpose of this study is to explore the effects of acupuncture-balanced anesthesia on the postoperative recovery of gastrointestinal function, on anesthesia strategies for abdominal surgery, on postoperative pain treatment, and on any associated complications or alterations in immune function. We further seek to verify the protective effects of transcutaneous electrical acupoint stimulation (TEAS), to explore possible underlying neuroimmune–endocrine mechanisms, and to thereby develop an optimized acupuncture-balanced anesthesia strategy suitable for abdominal surgery. Together, these findings will provide a scientific basis for the clinical utilization of acupuncture-balanced anesthesia in the context of abdominal surgery.

**Methods/design:**

This study is a multicenter, large-sample, randomized placebo-controlled trial. All subjects will be patients undergoing elective gastric or colorectal surgery. In Part 1, these patients will be stratified according to surgical site (gastric or colorectal), and randomly divided into four groups based on different perioperative interventions: Con group, which will undergo sham TEAS before, during, and after surgery; T1 group, which will receive TEAS during the preoperative and intraoperative periods, and sham TEAS during the postoperative period; T2 group, which will receive TEAS during the preoperative period, sham TEAS during the intraoperative period, and TEAS during the postoperative period; and T3 group, which will receive TEAS before, during, and after operation. Part 2 of this study will focus solely on colorectal surgery patients. All patients will receive TEAS during the preoperative and intraoperative periods, and they will be randomized into four groups according to different postoperative treatments: Con′ group, which will not receive TEAS; T1′ group, which will receive sham TEAS; T2′ group, which will receive 5-Hz TEAS; and T3′ group, which will receive 100-Hz TEAS. Venous blood (5 ml) will be used to measure immunological and inflammatory indexes both at the preoperative stage prior to TEAS and 4–5 days after operation. The primary outcome will be the time to first bowel sounds after surgery. Secondary outcomes will include gastrointestinal functional recovery, analgesic efficacy during the postoperative period, acupuncture-balanced anesthesia efficacy, postoperative nausea and vomiting, and postoperative complications.

**Discussion:**

This study is designed to investigate the clinical value of TEAS during various perioperative periods in those undergoing abdominal surgery, with the overall goal of evaluating the clinical value and advantages of acupuncture-balanced anesthesia, and of providing new strategies for improving patient prognoses.

**Trial registration:**

Chinese Clinical Trial Registry, ChiCTR-TRC-14004435. Registered on 26 March 2014.

**Electronic supplementary material:**

The online version of this article (10.1186/s13063-019-3558-2) contains supplementary material, which is available to authorized users.

## Background

The clinical application of acupuncture and the scientific basis for acupuncture are of increasing interest, as evidenced by a rapid increase in the number of acupuncture-related studies over the past decade. Acupuncture is a form of traditional Chinese medicine, with acupuncture analgesia being one of the most studied and best understood varieties [1]. Despite previous research, studies to date on the protective benefits of acupuncture have failed to properly assess long-term patient prognosis. As such, well-controlled trials exploring these long-term effects have the potential to help decrease medical costs of gastrointestinal surgery and reduce perioperative complications.

At present, acupuncture-related technologies include manual acupuncture, electroacupuncture, and transcutaneous electrical acupoint stimulation (TEAS). As electroacupuncture and TEAS can allow for accurate control of stimulation parameters, they are helpful for quantitative research and are thus favored by acupuncturists. For these reasons, we applied TEAS for use in our study.

Acupuncture-balanced anesthesia is an approach which combines acupuncture with anesthetics. It can significantly enhance the analgesic effect and reduce the dosage of anesthetics [2, 3], and can offer certain beneficial effects, such as alleviating preoperative anxiety [4] and reducing postoperative pain [5] and postoperative nausea and vomiting (PONV) [6]. By lowering the need for anesthetic usage, TEAS may thus allow for better intraoperative circulatory and respiratory stabilization [7], enhanced surgery recovery, reduced complication rates, and better organ functionality [8].

Acupuncture-balanced anesthesia has been found to help protect the brain [9, 10], heart [11], and other tissues, with positive benefits for gastrointestinal function. Acupuncture can regulate vasoactive intestinal peptide levels and improve gastrointestinal motility by relaxing the gastrointestinal smooth muscle [12]. Other studies have found that acupuncture can be helpful as a means of restoring gastrointestinal barrier function [13], and electroacupuncture pretreatment can decrease acetylsalicylic acid-induced ulcer severity by decreasing gastric acidity and increasing cyclooxygenase (COX)-1 and COX-2 expression [14]. The brain–gut axis is a complex network that maintains gastrointestinal homeostasis [15]. Fang et al. [16] found that acupuncture can relieve symptoms of functional dyspepsia, normalizing the function of the brain–gut axis as it pertains to this disease.

A series of animal experiments have revealed that acupuncture can further modulate the regulation of cellular and humoral immunity [17, 18], balancing Th1/Th2/Th17/Treg Th cell subset responses [19] and potentially improving mucosal immune protection by increasing immunoglobulin A secretion [20].

Acupuncture-balanced anesthesia can further reduce stress responses in elderly patients undergoing laparoscopic cholecystectomy, improving their hemodynamic stability [21].

Despite this previous evidence, the majority of studies of acupuncture-balanced anesthesia today have been of a single-center design, and have not assessed relevant clinical prognostic indicators. In addition, most of these acupuncture studies have been limited to the intraoperative period, without fully assessing benefits during the perioperative period. Therefore, there are many vital research questions pertaining to the effects of acupuncture-balanced anesthesia on organ protection that remain to be answered, including the following: whether acupuncture can improve the general condition of patients during the preoperative period (e.g., by alleviating anxiety and pain); whether continuous acupuncture treatment is beneficial for patients’ postoperative recovery, including gastrointestinal function recovery, postoperative pain management, PONV, and postoperative complications; and how perioperative acupuncture influences long-term prognosis, including quality of life and mortality. By studying these key unknown questions, it would be possible to develop novel breakthroughs and extend the clinical application of acupuncture-balanced anesthesia.

## Methods/design

### Design

This multicenter, large-sample, randomized placebo-controlled trial will be conducted in five hospitals at four institutions. The study protocol has been approved by the ethics committee at Peking University People’s Hospital. Patients undergoing elective gastric or colorectal surgery will be selected. Informed consent will be obtained before randomization. This protocol can only be amended with approval from the ethics committee, leading to an appropriate update in the Chinese Clinical Trial Registry. The findings of the study will be disseminated in academic journals and conference presentations.

### Patient population and methodology

#### Inclusion criteria

Patient inclusion criteria for this ongoing trial are as follows: age 18–75 years; consecutive patients undergoing elective abdominal surgery; body mass index 18–31 kg/m^2^; American Society of Anesthesiologists grade I–III; and signed informed consent.

#### Exclusion criteria

Patients meeting any of the following criteria will be excluded from this trial: scars or sensory impairments around the acupoints of interest; infections around the acupoints of interest; peripheral nerve injuries; history of spinal surgery; participation in other clinical trials within the past 4 weeks; inability to understand Numeric Rating Scales (NRS) scores or rejection of patient-controlled intravenous analgesia (PCIA); patients with a cardiac pacemaker; females in periods of menstruation, pregnancy, or breastfeeding; patients with preoperative pain or a history of analgesic usage; patients with mental or neurological diseases; patients who require an intraoperative colostomy; heavy drinking, defined by the National Institute on Alcohol Abuse and Alcoholism as more than three standard drinks (containing 14 g of pure alcohol) per day for women and more than four standard drinks per day for men [22]; patients returning to the intensive care unit; patients with allergies or a history of steroid usage; patients who develop serious intraoperative complications will be excluded after operation (such as blood loss > 2000 ml; brain, heart, and lung-related complications); patients with a history of liver or kidney disease; serum K^+^ > 5.5 mmol/L or < 3.0 mmol/L; preoperative hemoglobin < 7 g/dl; or patients deemed unsuitable by the researchers.

### Randomization and blinding

A random allocation sequence will be implemented using a remote network electronic randomization system (CIMS® Brightechm, Chengdu, China), according to preset conditions and procedures, thus ensuring correct randomization. Random codes will be generated by an independent statistician using a stratified block randomization scheme. Surgical site (gastric or colorectal) will be considered a stratifying factor. Participants will be randomly assigned to each group based on their sequence of visitation to the study centers.

Allocations of subjects will be kept confidential, without the possibility of unblinding except in emergencies and with approval from the principal investigator as a result of serious adverse events in patients. After unblinding, patient trial treatment will be discontinued, and the results of the treatment will be notified to the inspector, with the details, dates, and appropriate signatures being included in a case report form (CRF).

The investigators will be responsible for enrolling patients. Once a patient is successfully enrolled, the practitioners will register and randomize the patient in the randomization system. The practitioners will be aware of the allocation in order to provide treatment for the participants, while the participants, outcome assessors, and data analysts will be blinded to the treatment allocation. Practitioners and outcome assessors will not communicate with each other.

Sham TEAS will be set to 1 mA lower than the current that participants are able to just feel. This is a very strict and quantifiable “minimal stimulus” method in acupuncture-related research [23], and there are published articles supporting this design [24, 25]. In order to maximize participants’ blinding, the same stimulators, electrodes, and acupoints will be selected. The stimulators will be turned on, and a 30-min countdown will be set up for all participants. We will tell all participants that treatment parameters vary on an individual basis, and as such they may have different feelings regarding the treatment.

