**Fig. 1 Fig1:**
[figure not shown]
Part 1 trial flowchart. For group details, see Table 1. d days, TEAS transcutaneous electrical acupoint stimulation

Preliminary data analysis based on Part 1 suggest potential benefits of postoperative TEAS for gastrointestinal function recovery, but the effect was slight. Previous animal experiments have suggested that 5 Hz is more effective than 2/100 Hz as a means of promoting the recovery of gastrointestinal function, so we will adjust the study stimulation frequency before initiating Part 2 of this study protocol. In Part 2, all patients will be stimulated at 2/100 Hz (Hegu (LI4) and Neiguan (P6) acupoints; bilateral) before and during surgery. After surgery, patients will receive no TEAS, sham TEAS, 5-Hz TEAS, or 100-Hz TEAS. The same acupoints will be assessed in this trial. In order to observe colorectal function recovery more specifically, Part 2 of this study will focus only on patients undergoing colorectal surgery. The test groups for Part 2 of this study are presented in Table 2, with a study design flowchart shown in Fig. 2.

**Table 2 Tab2:** Part 2 test groups

Group	Sample size (*n*)	Intervention		
		Preoperative	Intraoperative	Postoperative
Con′	100	2/100 Hz TEAS	2/100 Hz TEAS	Control
T1′	100	2/100 Hz TEAS	2/100 Hz TEAS	Sham TEAS
T2′	100	2/100 Hz TEAS	2/100 Hz TEAS	5 Hz TEAS
T3′	100	2/100 Hz TEAS	2/100 Hz TEAS	100 Hz TEAS

*TEAS* transcutaneous electrical acupoint stimulation

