### Primary/secondary efficacy endpoints

A covariance model (ANCOVA) will be fitted, with primary endpoint changes from baseline serving as the dependent parameter, and with treatment group, baseline, and study site serving as fixed effects for consideration of site–treatment interactions. For ordinal and categorical variables, a Cochran–Mantel–Haenszel (CMH) test will be used, with study site as a stratifying factor.

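### Part 1 randomization is stratified by gastric or colorectal surgery, but the stated efficacy analyses leave that factor out

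*Protocol article*

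**What the plan says.** Under Randomization and blinding, the protocol article states: "Random codes will be generated by an independent statistician using a stratified block randomization scheme". The one factor it names follows: "Surgical site (gastric or colorectal) will be considered a stratifying factor". The Methods/design part of the Abstract places this in the first part of the trial: "In Part 1, these patients will be stratified according to surgical site (gastric or colorectal".

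Under Primary/secondary efficacy endpoints, the ANCOVA is described "with treatment group, baseline, and study site serving as fixed effects". Ordinal and categorical outcomes get a CMH test "with study site as a stratifying factor". The Statistical analysis section adds ANOVA, Kruskal–Wallis and chi-square tests, with no stratifier.

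Trial status reports that both recruitment and data analysis of Part 1 are complete.

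**The concern.** Stratified blocks force the arms to be balanced on surgical site, so differences between gastric and colorectal patients largely drop out of the treatment contrast. An analysis without the factor still counts those differences as residual noise. Its standard error then describes a less precise trial than the one that was run: intervals are too wide, p values too large, and some of the gain from stratifying is lost.

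This is more than a detail that an article would leave to a fuller document, because the article does list its model terms and its CMH stratum. The list omits the one named randomization factor and includes study site, which is not named as one.

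**Working it through.** **Inputs.** From Sample size calculations: effect 60.320 − 51.558 = 8.762 h, SD 17.8 h, ratio 3:2, power 90%, and 120 and 80 per group after allowance for 10% drop-out. From Statistical analysis: two-sided α = 0.05. Assumed, because the documents do not give them: a gastric–colorectal difference D of 0 to 12 h, and a 50/50 mix (30/70 as a check).

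**The plan's own figure first.** Smaller group: (1 + 1/1.5) × [17.8 × (1.960 + 1.282)/8.762]² = 72.3, rounded up to 73. Larger group: 73 × 1.5 = 109.5, rounded up to 110. Both match the protocol. A one-sided test would give 59 and 89, which does not.

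**Baseline power.** 80 and 120 less 10% leave 72 and 108 evaluable. The nominal SE is 17.8 × √(1/72 + 1/108) = 2.708 h, and power is Φ(8.762/2.708 − 1.960) = 89.9%.

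**Effect of leaving surgical site out.** The total SD is held at 17.8 h and the factor is balanced by design.
- Variance share: s = p(1 − p)D²/17.8², with p the proportion having one type of surgery.
- Nominal SE over true SE: r = 1/√(1 − s).
- True type I error: 2[1 − Φ(1.960 r)].
- Power without the term: Φ(8.762/SE_true − 1.960 r). Power with it: Φ(8.762/SE_true − 1.960). SE_true = 2.708/r.

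Example, D = 12 h, p = 0.5:
- s = 36/316.84 = 0.114 and r = 1.062.
- Type I error = 2[1 − Φ(2.082)] = 0.037.
- SE_true = 2.550 h and 8.762/2.550 = 3.436.
- Power is Φ(3.436 − 2.082) = 91.2% without the term and Φ(3.436 − 1.960) = 93.0% with it.

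| D (h) | s | r | Type I error, site omitted | Power, omitted | Power, included | Loss (points) |
|---|---|---|---|---|---|---|
| 0 | 0.000 | 1.000 | 0.050 | 89.9% | 89.9% | 0.0 |
| 3 | 0.007 | 1.004 | 0.049 | 90.0% | 90.1% | 0.1 |
| 6 | 0.028 | 1.015 | 0.047 | 90.2% | 90.7% | 0.5 |
| 9 | 0.064 | 1.034 | 0.043 | 90.6% | 91.7% | 1.1 |
| 12 | 0.114 | 1.062 | 0.037 | 91.2% | 93.0% | 1.8 |

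With a 30/70 mix the largest loss, at 12 h, is 1.5 points.

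**Check by simulation.** 20,000 linear-model runs with exact balance agree. At 12 h, type I error is 0.036 without the term and 0.050 with it, and power is 90.8% against 92.7%. At 6 h, the figures are 0.046 against 0.050 and 89.7% against 90.3%.

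**Smaller treatment effect.** The power loss depends on the effect assumed. The article calls the preliminary Part 1 effect of postoperative stimulation slight but gives no figure. At an assumed 5.5 h, the loss is 1.1, 2.6 and 4.8 points for D = 6, 9 and 12 h. Type I error and interval width do not depend on the treatment effect and stay as tabulated.

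**The case against.** The strongest reply is that the omission does little harm and errs on the safe side. The treatment estimate is unbiased, type I error is at or below 5%, and at the planned effect power does not fall below 89.9% anywhere in the assumed range. The loss exists only if surgical site is prognostic, for which the documents offer no figure. The ANCOVA also carries baseline and study site, which may already absorb some of the same variance. The SD of 17.8 h is the larger of two from a single-center preliminary test whose case mix is not stated. All of this stands, and it limits the size of the point. It does not remove the mismatch. Nor can study site be read as surgical site: the same sentence speaks of site-by-treatment interactions, and the trial "will be conducted in five hospitals at four institutions".

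Timing is a second fair objection. Part 1 has been analysed, so a new model term comes after results were seen. That governs how the adjusted result is reported. The reason for adjusting still comes from the randomization and not from the data.

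A reader might go further and infer that Part 2 is effectively unstratified, because "Part 2 of this study will focus only on patients undergoing colorectal surgery" makes the named factor constant there, and so propose re-blocking by hospital. The documents do not support this:
- The Abstract ties surgical-site stratification to Part 1, so a constant factor in Part 2 contradicts nothing.
- "Participants will be randomly assigned to each group based on their sequence of visitation to the study centers" leaves open whether sequences run by centre.
- Blocks without strata are valid, and study site is in the model. If hospital were unstratified across five centres with about 90 evaluable per arm, simulated power would be about 90.4% on average, against 91.0% with perfect balance.
- Recruitment was expected to end in July 2019, the month of publication, so re-blocking would be largely moot.

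**Conclusion.** The point holds for Part 1: a factor used to stratify the randomization is missing from the stated efficacy analyses. It is a minor to moderate point. Over an assumed 0 to 12 h gastric–colorectal difference, with a 50/50 mix and SD 17.8 h, type I error is 0.050 down to 0.037, intervals are 0% to 6% too wide, and power at the planned 8.762 h effect is 0 to 1.8 points lower than it need be. There is no bias and no effect on sample size. The power loss would be larger if the true treatment effect were smaller than planned.

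A reader might also infer much larger losses by taking the assumed difference to 18 h, where type I error would be 0.023. That is about one full SD and about twice the planned treatment effect, and nothing in the documents supports it. The point does not extend to how Part 2 was randomized.

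**What to change.** Add surgical site (gastric or colorectal) as a fixed effect in the Part 1 ANCOVA, and form the CMH strata from surgical site and study site together. With five hospitals that gives at most 2 × 5 = 10 strata, on average 400/10 = 40 of the planned Part 1 patients each, which is workable.

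Report the result as a design-based adjusted analysis, state that it was added after the first Part 1 analysis, and show it next to that analysis. Keep hospital in the Part 2 model as planned.

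The cost is one term per analysis, using a variable already recorded for randomization. The small downside is the labelling: the adjusted Part 1 result cannot be presented as the analysis planned beforehand. If the change is treated as a protocol amendment, the Design section requires ethics approval and a registry update.

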### Interventions

For this study, the bilateral Hegu (LI4), Neiguan (P6), Zusanli (ST36), and Sanyinjiao (SP6) acupoints will be selected. A HANS 100B (four conductors, eight electrodes) transdermal acupoint electrical stimulation apparatus (Nanjing Jisheng Company) will be used to stimulate the bilateral Hegu (LI4) and Neiguan (P6) acupoints for 30 min before anesthetic induction and during the intraoperative period until suturing of the surgical site is completed. The Hegu (LI4), Neiguan (P6), Zusanli (ST36), and Sanyinjiao (SP6) acupoints will be stimulated at 9:00 a.m. and 3:00 p.m. each day on the 1st, 2nd, and 3rd postoperative days. Each treatment will last for 30 min. Stimulation parameters will be as follows: a dense-disperse frequency of 2/100 Hz, with true stimulation being the maximum tolerable setting for a patient, and with sham simulation being 1 mA lower than the current that patients are able to just feel. The test groups for Part 1 are presented in Table 1, and a study design flowchart is shown in Fig. 1.

**Table 1 Tab1:** Part 1 test groups

Group	Sample size (*n*)	Intervention
Con	80	Sham TEAS before, during, and after operation
T1	120	Preoperative and intraoperative TEAS, and postoperative sham TEAS
T2	80	Preoperative TEAS, intraoperative sham TEAS, and postoperative TEAS
T3	120	TEAS before, during, and after operation

*TEAS* transcutaneous electrical acupoint stimulation

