### Sample size calculations

This study utilizes a superiority design, and the sample size has been calculated according to the primary endpoint of time to first bowel sound recovery following surgery. Based on a single-center preliminary test, this recovery time was 60.320 ± 9.8167 h in sham TEAS-treated individuals and 51.558 ± 17.8499 h in patients who received TEAS during all phases of the perioperative period. Therefore, the difference between the two groups was 8.762 h. Adopting a conservative point of view, the larger standard deviation of 17.8 was used to calculate the optimal sample size. In Part 1, according to a ratio of 3:2 and a power of 90%, a total of 110 and 73 patients were needed per group. To additionally account for a 10% drop-out rate, these case numbers were increased to 120 and 80, respectively. The reason for this unbalanced design between the groups was that both the T1 and T3 groups underwent TEAS before and during the operation, and thus have the potential to achieve a better therapeutic outcome. To ensure maximal possible patient protection, 80 cases were included in the Con and T2 groups, while 120 cases were included in the T1 and T3 groups.

In Part 2, as all patients received the same preoperative and intraoperative interventions, the allocation ratio was altered to 1:1:1:1, with 100 participants per group.

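### As the article reads, Part 2 patients are allocated at enrollment and practitioners know the arm, although nothing given differs by arm until the first postoperative session

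*Protocol article*

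**What the plan says.** The section on randomization and blinding describes one procedure and makes no distinction between Part 1 and Part 2. Investigators enroll, and then "Once a patient is successfully enrolled, the practitioners will register and randomize the patient in the randomization system". The reason for disclosure is stated: "The practitioners will be aware of the allocation in order to provide treatment for the participants". Blinding covers other people: "while the participants, outcome assessors, and data analysts will be blinded to the treatment allocation". Practitioners and assessors are not to communicate.

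For the Part 2 treatment, the Interventions section (text below Fig. 1) says "In Part 2, all patients will be stimulated at 2/100 Hz" before and during surgery, and then "After surgery, patients will receive no TEAS, sham TEAS, 5-Hz TEAS, or 100-Hz TEAS". Table 2 agrees: the preoperative and intraoperative columns are identical in all four rows. The only postoperative timetable in the article starts at 9:00 a.m. on postoperative day 1. Intensity is not a fixed current; it is defined as 2/100 Hz "with true stimulation being the maximum tolerable setting for a patient".

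The sample size section gives the common background as the reason for equal allocation: "In Part 2, as all patients received the same preoperative and intraoperative interventions, the allocation ratio was altered to 1:1:1:1", with 100 patients per group.

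The exclusion criteria include three that are settled during or just after the operation: need for an intraoperative colostomy, return to intensive care, and serious intraoperative complications. Only the last is expressly applied after the operation.

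**The concern.** In Part 1 the arms already differ before or during surgery, so practitioners need the allocation by then. Part 2 carries the same rule into a design where that reason does not apply until the patient is back from theatre.

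Two things are then exposed without need. First, a Part 2 difference can be put down to the postoperative treatment only if the earlier phase was equal across arms. That phase is tailored to each patient, and it may be delivered by someone who knows whether the patient will later get nothing, sham, 5 Hz or 100 Hz. The stated safeguards protect outcome assessment, not delivery of the background treatment. Second, patients removed for events in theatre are removed after randomization. Some allocated patients then never reach the randomized comparison, and the decision to remove them may be made when the arm is known.

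**Working it through.** **1. Is the arm needed before surgery in Part 2?**

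| Phase | Con′ | T1′ | T2′ | T3′ | Does treatment depend on arm? |
|---|---|---|---|---|---|
| Preoperative | 2/100 Hz | 2/100 Hz | 2/100 Hz | 2/100 Hz | No |
| Intraoperative | 2/100 Hz | 2/100 Hz | 2/100 Hz | 2/100 Hz | No |
| From postoperative day 1 | None | Sham | 5 Hz | 100 Hz | Yes |

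The source is Table 2 with the postoperative timetable in Interventions. No separate Part 2 timetable is given, so I take the same one to apply. The stated reason for disclosure starts to hold only in the last row.

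**2. Does any text delay allocation or disclosure in Part 2?** None that is shown. The rule ties randomization to successful enrollment and names practitioners as aware of the arm.

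**3. Is there a route by which the background could differ?** Yes, a possible one: the current is set for each patient and not fixed in advance.

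**4. Where do the in-theatre exclusions fall?** With allocation at enrollment, all three come after randomization. Because the assigned treatment is still the same at that point, the arms themselves cannot cause these events. The cost is uneven loss, plus any influence of knowing the arm on the decision to exclude. With allocation after surgery, all three become pre-randomization exclusions.

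**5. What would a background shift do?** The documents give no figure for it, so this is an illustration on assumed shifts. The SD and pilot difference come from the sample size section, and they do reproduce its Part 1 figure. For the smaller arm at 3:2, two-sided 5% and 90% power, n = (1 + 1/1.5) × [17.8 × (1.960 + 1.282) / 8.762]² = 72.3, so 73, and 1.5 × 73 = 109.5, so 110, as stated.

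For Part 2, assume no true postoperative effect and a background shift of b hours between two arms. With SE = 17.8 × √(2/n), the rejection probability is Φ(b/SE − 1.96) + Φ(−b/SE − 1.96). For n = 100, SE = 2.517 h; for n = 90 (10% drop-out), SE = 2.653 h.

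| Assumed b (h) | b as share of 8.762 h | Rejection, n = 100 | Rejection, n = 90 |
|---|---|---|---|
| 0 | 0% | 0.050 | 0.050 |
| 1 | 11% | 0.068 | 0.066 |
| 2 | 23% | 0.125 | 0.117 |
| 3 | 34% | 0.222 | 0.204 |
| 4 | 46% | 0.356 | 0.326 |

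The 8.762 h is the pilot difference between TEAS in all phases and sham. A 3 or 4 h shift from intensity differences within one part of the treatment would be a large share of that and is hard to credit. At 1 h the inflation is small. A larger trial would not remove such a bias.

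**6. Does the remedy change N?** No. Moving the allocation step leaves 100 per arm as planned.

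**The case against.** The article contains no contradiction or false statement here, and several links are weaker than they may look.

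- **Timing.** The randomization paragraph is generic. The Part 2 flowchart and the SPIRIT figure are not shown, and either might place allocation elsewhere. Allocation before surgery is the natural reading of the text, not a demonstrated fact. This stands as a caveat.
- **Same person.** A reader might infer that the individual who randomizes also gives the theatre sessions and the ward sessions. The text says only practitioners, in the plural, and does not say who gives which session. The point must rest on practitioners who may know the arm.
- **Operator control of intensity.** A reader might infer that the operator sets the dose freely. The ceiling is the patient's own tolerance, and patients are to be blinded. This narrows the route but does not close it, because someone still turns the current up and decides when the ceiling is reached. How the current is handled under anesthesia is not stated.
- **Coaching, anesthetic handling, center differences.** A reader might extend the concern to these. Nothing shown gives TEAS practitioners control of the anesthetic, which follows one stated protocol in both parts. Study site is also in the analysis model. None of this belongs in the point.
- **Cancelled or converted operations.** The documents do not mention these; the listed exclusions are the firm basis.
- **The equality statement.** The clause "as all patients received the same preoperative and intraoperative interventions" explains the change of ratio. It concerns assigned interventions and does not claim equal delivered current.
- **Reach.** Recruitment was expected to end in July 2019 and the article appeared on 29 July 2019, so few or no patients may remain.

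What survives is narrow but sound: on the shown text, disclosure before surgery serves no purpose in Part 2, and delaying it costs little.

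**Conclusion.** The point holds as a low-cost improvement to the Part 2 design, not as an error that invalidates it. Allocation at enrollment opens a route for performance bias in the common background treatment and puts exclusions settled in theatre after randomization, with no offsetting need.

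The size is unknown. The Part 2 plan covers 400 patients (4 × 100), but that counts patients under the rule, not patients affected. The rejection rates above are conditional on assumed shifts and are not estimates. A reader might infer that the Part 2 background did differ by arm; nothing shown supports that.

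The conclusion rests on three assumptions: that the single randomization rule applies to Part 2 as written, that the postoperative timetable is the same in Part 2, and that the figures not shown do not set a later allocation. It does not apply to Part 1.

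**What to change.** **Part 2 patients still to be recruited.** Keep consent and baseline before surgery. Carry out the allocation in the electronic system after the operation, once eligibility is confirmed and before the first postoperative session. If patients must be registered earlier, have the system withhold the arm until then. Withholding protects delivery equally well. It leaves the in-theatre exclusions formally after randomization, but decided without knowledge of the arm.

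**Part 2 patients already randomized.** If the pre- and intraoperative current was recorded, tabulate and compare it by arm. Report post-randomization exclusions by arm with reasons. This may be the only part still feasible.

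**If the full protocol already allocates after surgery in Part 2,** a sentence saying so in the randomization section is enough.

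**Cost.** A short amendment and what should be a small change to the existing system. Practitioners log in later, and some consented patients are never randomized. A change in mid-recruitment leaves two allocation regimes within Part 2, so the date of change should be recorded and reported. Sample size is unchanged.
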